#### Method of Data Analysis

Data will be collected from a chart review and recorded in a database spreadsheet. Statistical analysis will be performed to calculate data collected in this study. Results will be reported using summary tables and will be displayed for each treatment arm. For categorical variables, frequencies and percentages will be presented. For continuous variables, the number of subjects, mean, standard deviation, minimum, 25th percentile, median, 75th percentile and maximum will be presented. Reported differences will include standard errors and 95% CI.

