## Results

Preliminary data analysis for the year 2017 has been completed. Compared to a baseline 2016 survival rate of 47.0%, from 2017 to 2018, CS survival rates were increased to 57.9% (81/140) and 81.3% (26/32), respectively (*P*=.01 for both). Survival in acute MI with CS increased from 52.6% (30/57) to 75.0% (12/16) and in acute decompensated HF from 61.4% (51/83) to 87.5% (14/16). For 2017, CS threshold markers at 12 hours (lactate<3.0 mg/dL, CPO>.6 W, PAPi>1.0) overall survival was 80% (72/90), 93.6% (73/78) and 74% (71/96), respectively. For 2018, CS threshold markers at 12 hours (lactate<3.0 mg/dL, CPO>.6 W, PAPi>1.0), overall survival was 92.3% (24/36), 92% (23/25) and 85.2% (23/27), respectively. Use of RHC was associated with 14% greater survival. Decreases of 5 and 10 hours in the time to implement MCS were associated with increased survival 53.6% and 135.8%, respectively. Age was associated with survival; patient’s ≥75 years old had higher risk of death (odds ratio 3.43, 95% CI 1.20-9.78).

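### The time-to-MCS result is printed as a percentage increase in survival with no scale named; the 10-hour figure cannot be that at any overall or etiology rate reported, and the pair is one coefficient and its square, most plausibly an odds ratio

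*Protocol article*

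**What the plan says.** The Results section of the protocol article gives one quantitative finding on the speed of mechanical circulatory support (MCS): "Decreases of 5 and 10 hours in the time to implement MCS were associated with increased survival 53.6% and 135.8%, respectively". No model, effect scale, reference survival, number of patients or interval goes with it. The same section reports a 2016 baseline survival of 47.0% and says that afterwards "CS survival rates were increased to 57.9% (81/140) and 81.3% (26/32), respectively" for 2017 and 2018. By etiology, survival was 52.6% and 75.0% in acute myocardial infarction and 61.4% and 87.5% in acute decompensated heart failure. The sentence after the MCS result does name its scale: "patient’s ≥75 years old had higher risk of death (odds ratio 3.43, 95% CI 1.20-9.78".

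Method of Data Analysis promises: "Reported differences will include standard errors and 95% CI".

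**The concern.** Read as written, the sentence says that survival rises by about half when MCS starts 5 hours sooner and more than doubles when it starts 10 hours sooner. With survival already near or above one half in every overall and etiology group reported, a doubling leaves no room below 100%. The two figures also look like a dose-response seen at two points, when they may be one fitted slope printed twice.

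Rapid initiation of MCS is part of the Hypothesis and of the third objective in the Abstract. Timely MCS is credited in the Abstract's Conclusions and again in the Discussion. This sentence is the only number behind those statements, so a reader who takes it at face value would carry away an effect on survival that the reported rates do not allow at 10 hours.

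**Working it through.** **Inputs.** From Results: increases of 53.6% (5 h) and 135.8% (10 h), that is, multipliers of 1.536 and 2.358; overall survival 47.0% (2016), 81/140 = 57.9% (2017), 26/32 = 81.3% (2018); etiology rates 30/57 = 52.6% and 51/83 = 61.4% (2017), 12/16 = 75.0% and 14/16 = 87.5% (2018). The Abstract attaches different counts to the same overall percentages. The Results counts reproduce the percentages and are used here. Survival after late MCS, the proper reference, is not given; 20% and 40% are used below as assumptions.

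**Step 1: do the two figures come from one coefficient?** If the effect of time is linear on a log scale, the 10-hour multiplier is the square of the 5-hour multiplier. 1.536² = 2.359. Allowing for rounding of 53.6%, the range is 1.5355² = 2.3578 to 1.5365² = 2.3608. The printed 2.358 lies inside it (√2.358 = 1.5356). The pair therefore reproduces as one multiplicative slope of 1.536^(1/5) ≈ 1.09 per hour.

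**Step 2: can they be changes in survival probability?** For reference survival p, the absolute reading is p + x and the relative reading is p(1 + x).

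| Reference p | 5 h absolute: p + 53.6 | 5 h relative: p × 1.536 | 10 h relative: p × 2.358 |
|---|---|---|---|
| 47.0% | 100.6% | 72.2% | 110.8% |
| 52.6% | 106.2% | 80.8% | 124.1% |
| 57.9% | 111.5% | 88.9% | 136.4% |
| 61.4% | 115.0% | 94.4% | 144.9% |

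At the three 2018 rates every one of these readings exceeds 100%; the smallest is 75.0% × 1.536 = 115.2%. The limits are 1/1.536 = 65.1% for the 5-hour relative reading and 1/2.358 = 42.4% for the 10-hour one. A gain of 135.8 points is impossible from any starting value.

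**Step 3: what would the figures mean as odds ratios?** With o = p/(1 − p), new survival is q = OR·o/(1 + OR·o). For p = 81/140, o = 81/59 = 1.373. At 5 h, 1.536 × 1.373 = 2.109 and q = 2.109/3.109 = 67.8%. At 10 h, 2.358 × 1.373 = 3.237 and q = 3.237/4.237 = 76.4%. The last column divides the printed percentage by the relative gain q/p − 1.

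| Reference p | 5 h: survival (gain; relative) | 10 h: survival (gain; relative) | Printed ÷ relative gain, 5 h and 10 h |
|---|---|---|---|
| 47.0% | 57.7% (10.7 points; 22.7%) | 67.6% (20.6 points; 43.9%) | 2.4 and 3.1 |
| 57.9% | 67.8% (10.0 points; 17.2%) | 76.4% (18.5 points; 32.0%) | 3.1 and 4.2 |
| 81.3% | 86.9% (5.7 points; 7.0%) | 91.1% (9.8 points; 12.1%) | 7.7 and 11.2 |
| 40% (assumed) | 50.6% (10.6 points; 26.5%) | 61.1% (21.1 points; 52.8%) | 2.0 and 2.6 |
| 20% (assumed) | 27.7% (7.7 points; 38.7%) | 37.1% (17.1 points; 85.4%) | 1.4 and 1.6 |

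**Step 4: another scale.** If the multiplier instead divides the hazard of death, new survival is p^(1/1.536) and p^(1/2.358). From 57.9% this gives 70.0% and 79.3%, relative gains of 21.0% and 37.0%. From an assumed 20% the relative gains would be 75.4% and 152.7%, larger than those printed. The direction of any misstatement therefore depends on the scale.

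**The case against.** The strongest reply is that the right reference is survival in patients who received MCS late, and the article does not report it. The 57.9% covers all 2017 shock patients. If late-MCS survival were 42.4% or less, a 135.8% relative rise would be arithmetically possible. This stands, and it limits the claim to the overall and etiology rates that are printed. It does not rescue the sentence: the reader is given no such reference, and even an assumed 40% would imply 40% × 2.358 = 94.3% survival with MCS 10 hours earlier, above every survival rate in Results.

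Three stronger readings are tempting and are not supported.

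- A reader might infer that both figures are impossible. As a relative increase, 53.6% is possible at 47.0%, 52.6%, 57.9% and 61.4%.
- A reader might take the odds ratio as established. The squared relation shows only log-linearity; a log-linear risk model or a hazard model gives the same pattern. The age result in the next sentence makes an odds ratio plausible but does not document it.
- A reader might say that the effect is overstated three- to four-fold. That holds only for an odds ratio and a 57.9% reference. Over the references in Step 3 the factor runs from 1.4 to 11.2.

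It is also fair to say that the analysis is labelled preliminary, that a condensed article may omit model detail, and that giving one coefficient at two increments is not in itself an error. The missing interval is therefore a lesser matter. The wording of the result is not: it is something the article states, not something it leaves to a fuller document.

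**Conclusion.** The point holds as a misworded result. The 10-hour figure cannot be a change in survival probability at any overall or etiology rate in the article. The 5-hour figure cannot be an absolute change at those rates, though it could be a relative one up to a reference of 65.1%. The two figures are one coefficient and its square; this rests on the printed digits alone. That the coefficient is an odds ratio of about 1.54 per 5 hours is an inference.

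If the inference is right, calling the figures increases in survival overstates the effect at every reference, by an amount that depends on late-MCS survival: relative gains of 17% and 32% at 57.9%, 23% and 44% at 47.0%, and 7% and 12% at 81.3%. The sample size and the primary outcome are untouched. What changes is the only quantitative support for the article's statements about the speed of MCS.

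**What to change.** Confirm the scale from the existing model output. If it is an odds ratio, replace the sentence in Results with the odds ratio for survival per 5-hour shorter time to MCS (about 1.54 if confirmed), its 95% CI, and the numbers of MCS patients and deaths in the model. Do not describe it as a percentage increase in survival. Either drop the 10-hour figure or say that it is the same coefficient over 10 hours. If the scale turns out to be another one, name it and give the reference survival that makes the figures interpretable.

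No new data or analysis should be needed beyond rereading the output and rewording. The cost is that the stated effect will look less striking.

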**Results:**

Preliminary data analysis for the year 2017 has been completed. Compared to a baseline 2016 survival rate of 47.0%, from 2017 to 2018, CS survival rates were increased to 57.9% (58/110) and 81.3% (81/140), respectively (*P*=.01 for both). Study data will continue to be collected until December 31, 2018.

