#### Secondary Outcomes

Analysis of mortality by subgroup (age, sex, initial etiology, time to presentation, time to treatment, use of mechanical circulatory support, Incidence of major adverse cardiac and cerebrovascular events, and preservation of left ventricular function.

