## Discussion

Retrospective clinical outcomes (acute decompensated heart failure cardiogenic shock, acute myocardial infarction cardiogenic shock) demonstrated an increase in current survival rates when compared to pre-Cardiogenic Shock team initiation. IHVI site specific positive outcomes far exceeded the national average. Patients who had mechanical circulatory support did significantly better when the patient was younger than 75 years old at the time of intervention and when the mechanical circulatory support was initiated within five hours of the patients’ arrival at the IHVI. Yet to be analyzed is the significance of the type of intervention ECMO versus intracorporeal axial-flow (Impella).

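### Age is reported only as a split at 75, without counts or a consistent population; modelling it as continuous is a cheap improvement, worth about two to three times the information if risk rises smoothly with age

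*Protocol article*

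**What the plan says.** Under Secondary Outcomes the protocol article plans "Analysis of mortality by subgroup (age, sex, initial etiology, time to presentation, time to treatment", followed by further factors. It attaches no cut-off to age.

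The only age result is in the Results section, where patients of 75 or over "had higher risk of death (odds ratio 3.43, 95% CI 1.20-9.78"). The sentence gives no number of patients or deaths on either side of the cut, no covariates and no population.

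The Discussion returns to the same line but ties it to patients who had mechanical circulatory support, who "did significantly better when the patient was younger than 75 years old at the time of intervention". No figure accompanies that statement.

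The Results section calls the analysis preliminary, and the abstract says that data collection continues to the end of 2018. The final analysis is therefore still open.

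**The concern.** Age is a continuous predictor and a planned mortality factor. Reducing it to one split high in its range treats all patients below 75 as alike and all above as alike. Most of the information in age is then lost, unless risk really does change abruptly at 75. The interval shows how imprecise the result is: its upper limit is about eight times its lower limit (9.78/1.20 = 8.15).

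The reader also cannot tell how many older patients the odds ratio rests on, whether it is adjusted, or whether it describes all team patients or only those on mechanical support. The last is a matter of consistency within the article, since Results names no population and Discussion names a subset. At stake is how far a secondary finding can be trusted and reused.

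**Working it through.** **1. What the printed interval implies.** SE(log OR) = ln(9.78/1.20)/3.92 = 2.098/3.92 = 0.535. z = ln(3.43)/0.535 = 1.233/0.535 = 2.30, so the Wald P is 0.021. The geometric mean of the limits is √(1.20 × 9.78) = 3.43, so the interval is symmetric on the log scale, as a Wald interval should be.

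**2. Margins available.** The Results section gives survival in 2017 and 2018 as "57.9% (81/140) and 81.3% (26/32), respectively". Deaths are 140 − 81 = 59 and 32 − 26 = 6; pooled, there are 172 patients and 65 deaths. The etiology counts in the same section add up to these totals (57 + 83 = 140 and 30 + 51 = 81; 16 + 16 = 32 and 12 + 14 = 26). The abstract prints "57.9% (58/110) and 81.3% (81/140), respectively" instead, but 58/110 is 52.7% and 81/140 is 57.9%, so those counts do not match their own percentages.

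**3. Reproducing the odds ratio.** Every 2x2 table on each set of margins was tried, with OR = ad/(bc) and 95% CI = exp[ln OR ± 1.96 √(1/a + 1/b + 1/c + 1/d)].

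- Pooled margins (172 patients, 65 deaths) give exactly one match: 11 deaths and 6 survivors at 75 or over, 54 deaths and 101 survivors below. OR = (11 × 101)/(6 × 54) = 1111/324 = 3.429. SE = √(0.0909 + 0.1667 + 0.0185 + 0.0099) = 0.535. CI 1.202 to 9.781. Fisher P = 0.032. Mortality is 11/17 = 64.7% and 54/155 = 34.8%.
- The 2017 margins, the 2018 margins, the infarction and heart-failure subsets, and the abstract's counts give no exact match.

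**4. How unique the match is.** Of 15,651 pairs of total patients (60 to 200) and total deaths, 24 (0.15%) allow any exact match, so agreement by chance with the article's own pooled totals is unlikely. It is not impossible. A group of 94 with 37 deaths also fits: 12/19 older and 25/75 younger, OR = (12 × 50)/(7 × 25) = 3.429, SE = √(0.0833 + 0.1429 + 0.0400 + 0.0200) = 0.535, CI 1.20 to 9.78, mortality 63.2% and 33.3%. A mechanical-support subset of the 172 could be that size.

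**5. Fragility, on the pooled table.** With one death fewer in the older group and total deaths fixed (10/17), the OR is 2.60 (0.94 to 7.21), which includes 1.

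**6. Information kept by the cut.** For normally distributed age with log-odds linear in age, a cut with fraction p above it keeps φ(z)²/[p(1 − p)] of the information in continuous age, where z is the upper-p normal quantile.

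| Table | p | Information kept | Gain from continuous age |
|---|---|---|---|
| 17 of 172 | 0.099 | 0.34 | 2.9 |
| 19 of 94 | 0.202 | 0.49 | 2.0 |

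At p = 17/172, other age shapes give gains from 2.3 (right-skewed) to 4.2 (left-skewed).

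**7. Check by simulation (172 patients, normal age).** With log-odds rising linearly by 0.4 per standard deviation, power was 69% for continuous age and 31% for the split, and the ratio of squared mean z was 2.7. With a true step at the cut and odds ratio 3.43, power was 30% and 65%, and the ratio was 0.39.

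**The case against.** The strongest reply is that a condensed article may leave cut-offs and model form to a statistical analysis plan that is not shown, and that a split is consistent with a plan to analyse mortality by subgroup. That stands: the missing cut-off is not a defect in itself. A reader might infer that 75 was picked after the outcomes were seen. The documents do not support this, because the unseen plan may name the cut and nothing in the article describes a search over cuts.

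A reader might also take it as established that the odds ratio is crude and rests on 17 older patients. The article states neither. The pooled table is the leading candidate, but the Discussion speaks of a subset of unreported size, and the 94-patient table fits equally well.

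The efficiency gain is conditional as well: under a real threshold at 75 the split is the better analysis.

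Two further inferences go too far. The article labels its figure an odds ratio, and nowhere reads 3.43 as a ratio of risks. Nor does it propose to use the age split in the before/after comparison, so confounding there is not at issue.

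What the reply leaves standing is the missing counts and population for a printed result, the mismatch between Results and Discussion, and a more informative analysis available from data already abstracted.

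**Conclusion.** The point holds as a minor, cheap improvement to a secondary analysis. The age result is reported only as a split at 75, without the counts or population needed to judge it, and Results and Discussion do not agree on whom it covers. If age is roughly normal and log-odds are linear in age, the split keeps about 34-49% of the information for 10-20% of patients above the cut, so continuous age would yield about two to three times as much. That range rests on the two reconstructed tables, which are inferred rather than stated, and the advantage reverses if risk steps at 75. The primary survival comparison is not affected.

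**What to change.** In the final secondary mortality analysis, model age as a continuous variable, use a spline to check the shape, and report predicted mortality at chosen ages with 95% confidence intervals. Keep 75 or over versus under 75 as a descriptive line, with patients, deaths and absolute risks in each group. State whether that line covers all team patients or only those on mechanical circulatory support, and reconcile the Results and Discussion sentences accordingly.

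The cost is re-running one model on data already abstracted and adding a few counts. The drawbacks are that a single cut-off is easier to quote and that linearity has to be checked rather than assumed.

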## Discussion

Retrospective clinical outcomes (acute decompensated heart failure cardiogenic shock, acute myocardial infarction cardiogenic shock) demonstrated an increase in current survival rates when compared to pre-Cardiogenic Shock team initiation. IHVI site specific positive outcomes far exceeded the national average. Patients who had mechanical circulatory support did significantly better when the patient was younger than 75 years old at the time of intervention and when the mechanical circulatory support was initiated within five hours of the patients’ arrival at the IHVI. Yet to be analyzed is the significance of the type of intervention ECMO versus intracorporeal axial-flow (Impella).

## Abbreviations

ACS: acute coronary syndrome
ADHF: acute decompensated heart failure
AMI: acute myocardial infarction
CS: cardiogenic shock
CPO: cardiac power output
ECMO: extracorporeal membrane oxygenation
HIPPA: Health Insurance Portability and Accountability Act
ICU: intensive care unit
IHVI: Inova Heart and Vascular Institute
MI: myocardial infarction
NSTEMI: non-ST-segment elevation myocardial infarction
PHI: personal health information
RHC: right heart catheterization
STEMI: ST-segment elevation myocardial infarction
UID: unique identification
